#### Other measurements

Other measurements include demographic variables (e.g., age, gender, occupation etc.), the Effort Reward Imbalance Questionnaire – Short Form (ERI-SF) [75], the hope of improvement subscale of the German Patient Questionnaire on Therapy Expectation and Evaluation (PATHEV) [76] (adapted to the online training context), the German version of the Client Satisfactory Questionnaire (CSQ-8) [77,78] (adapted to the online training context), and a German questionnaire on the negative effects of psychotherapy (Ladwig, I., Rief, W., & Nestoriuc, Y.: Hat Psychotherapie auch Nebenwirkungen? Entwicklung des Inventars zur Erfassung Negativer Effekte von Psychotherapie (INEP) [Does psychotherapy have side effects? Development of an Inventory of Negative Effects of Psychotherapy (INEP)], submitted); adapted to the online training context). Approximately 30 minutes will be required to complete all questionnaires. For an overview of all outcome measures, see Table 2.

**Table 2 T2:** Outcome measures

	**T0**	**T1**	**T2**	**T3**	**T4**
					
Perceived Stress Scale	✔	✔	✔	✔	✔
Center for Epidemiological Studies Depression Scale	-	✔	✔	✔	✔
Hospital Anxiety and Depression Scales – Anxiety	-	✔	✔	✔	✔
Maslach Burnout Inventory – Emotional Exhaustion	-	✔	✔	✔	✔
Emotion Regulation Skills Questionnaire – Comprehension/Acceptance/Self-Support	-	✔	✔	✔	✔
Emotion Regulation Skills Questionnaire – General Distress	-	✔	✔	✔	✔
Attitudes Toward Seeking Professional Psychological Help Scale	-	✔	✔	✔	✔
Utrecht Work Engagement Scale	-	✔	✔	✔	✔
Recovery Experience Questionnaire – Psychological Detachment	-	✔	✔	✔	✔
Insomnia Severity Index	-	✔	✔	✔	✔
Penn State Worry Questionnaire – Ultra Brief	-	✔	✔	✔	✔
Trimbos/iMTA Questionnaire for Costs associated with Psychiatric Illness	-	✔	-	✔	(✔)
Quality of Life (EuroQol, SF-12)	-	✔	-	✔	(✔)
Demographic Variables Questionnaire	✔	-	-	-	-
Effort Reward Imbalance Questionnaire – Short Form	-	✔	-	-	-
Patient Questionnaire on Therapy Expectation and Evaluation (Online-Training)	-	✔	-	-	-
Client Satisfactory Questionnaire	-	-	(✔)	-	-
Questionnaire on Negative Effects of Online Trainings	-	-	(✔)	(✔)	(✔)
Potential Dropout Reasons	-	-	(✔)	-	-

*T0* Screening, *T1* Baseline, *T2* 7 weeks, *T3* 6 months, *T4* 12 months.

Assessments: ✔ = intervention and control group, (✔) = intervention group only

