### Aims of the study and hypotheses

In this study, we will investigate the efficacy and cost-effectiveness of a newly developed web-based stress-management training for stressed employees that is based on problem solving and emotion regulation. As a theoretical basis we have followed the transactional stress model of Richard Lazarus [35]. We hypothesize that participants in the intervention group will show a greater reduction in the primary outcome perceived stress from pre-test to post-test compared to a waitlist control group, and that this effect will be maintained over six months. We will conduct cost-effectiveness and cost-utility analyses from a societal perspective and hypothesize that the intervention will be cost-effective. Furthermore, explorative moderator analyses will be conducted.

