## Methods

### Study design

A randomized controlled trial with two conditions will be conducted. The intervention group will receive the web-based stress-management training “GET.ON Stress” and the control group will obtain access to this intervention after 6 months (see Figure 1). There will be no restriction with regard to the use of medication or other treatment as usual (TAU) (e.g., psychotherapy) in either of the groups. To control for potential confounding effects, TAU will be monitored.

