### Procedure

Participants will be recruited from the general working population via mass media (e.g., newspaper articles, television) between March and October 2013. Moreover, a major health insurance company (BARMER GEK) will support the recruitment process within their occupational health management program. On an open access website (http://www.geton-training.de) the interested people will be able to sign up to participate with an email-address. Applicants will receive further informational material concerning the study conditions and the training and will be asked to provide an email-address and a first and last name (which can be pseudonyms if desired) to participate. Afterwards, a link to the screening questionnaire will be sent. Applicants who are eligible for participation will be required to provide their informed consent and fill out the online baseline questionnaire. Subsequently, these participants will be randomly allocated to either the intervention or the control group. Participants will be informed of the outcome of the randomization and participants in the intervention group will receive immediate access to the GET.ON Stress training. Assessments will be scheduled at seven weeks and six months after randomization for both groups. However, the participants in the control group will receive the login data required to complete the training six months later than the intervention group. An extended follow-up for the intervention group is scheduled 12 months post-randomization.

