#### Quality of life

We will use the Short Form 12 (SF-12) [71] and the EuroQol (EQ-5D) [72] to assess quality of life. The SF-12 [71] covers eight health domains (physical functioning, role limitations, pain, general health perception, vitality, mental health, emotional role and social functioning) and allows for the calculation of two sum scores for physical and mental health. We will also use the EQ-5D which is a widely applied, valid and reliable measurement of quality of life and consists of five items related to mobility, self-care, common activities, pain/discomfort and anxiety/depression. Furthermore, this measurement contains a visual analogue scale concerning health state.

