#### Economic evaluation

We will perform an economic evaluation from a societal perspective that includes all relevant costs and outcomes. A cost-effectiveness analysis and a cost-utility analysis will be conducted. For cost-utility analyses, quality-adjusted life years (QUALYs) will be calculated. A non-parametric boot-strapping method with 95% confidence intervals in percentiles will be used to assess differences between the intervention and control group. We will compare the intervention and control groups in terms of incremental costs and incremental effects. Towards this end, we will calculate the incremental cost-effectiveness ratio (ICER). We will use bootstrapping (5,000 times) to test the robustness of the ICER and to quantify the uncertainty in the ratios. The results will be shown in a cost-effectiveness plane and in a cost-effective acceptability curve. Additionally, the robustness of the base-case findings will be tested with a multi-way sensitivity analysis.

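### EQ-5D and SF-12 are not collected at 7 weeks, so the QALY difference rests on baseline and month 6 alone and may be misestimated in either direction

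*Protocol article*

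**What the plan says.** The Quality of life section names the instruments: "We will use the Short Form 12 (SF-12) [71] and the EuroQol (EQ-5D) [72] to assess quality of life". Table 2, under Other measurements, sets their timing. The row "Quality of Life (EuroQol, SF-12" has a tick at T1 (baseline), a dash at T2, a tick at T3 and a bracketed tick at T4. The key dates T2 onward as "7 weeks, *T3* 6 months, *T4* 12 months", and a bracketed tick means "intervention group only".

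The 7-week assessment itself covers both arms. The Procedure section says "Assessments will be scheduled at seven weeks and six months after randomization for both groups", and Table 2 collects the stress, depression, anxiety, insomnia and other symptom scales from both arms at T2. The controlled period ends at month 6, because "the control group will obtain access to this intervention after 6 months" (Study design).

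The Economic evaluation section commits to a cost-utility comparison: "For cost-utility analyses, quality-adjusted life years (QUALYs) will be calculated". It gives no rule for turning utilities into QALYs. The Aims section expects a greater fall in perceived stress "from pre-test to post-test compared to a waitlist control group, and that this effect will be maintained over six months".

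**The concern.** A QALY is utility accumulated over time, so the between-group difference depends on when utility changes as well as where it ends. With controlled utilities only at weeks 0 and 26, the data cannot tell an early, sustained gain from a slow, steady one. Nor can they tell an early gain that faded from no gain at all. An assumed shape has to fill the gap.

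The shape that the trial expects for stress is an early change that then holds. If utility behaves likewise, a straight line from baseline to month 6 misses part of the gain. The QALY difference is the denominator of the cost-utility ratio, so the error carries into cost per QALY and the matching acceptability curve. The contact at which the missing value could be collected already exists.

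**Working it through.** **Inputs.** Utility times in both arms are weeks 0 and 26 (Table 2, taking 6 months as 26 weeks and a year as 52). The existing assessment without a utility measure is at week 7. T4 has no control group, so it adds nothing to the between-group contrast. The article gives no QALY or utility figure to reproduce. The sample size of 264 does not bear on this point.

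**Assumptions.** The between-group utility difference is 0 at baseline, U7 at week 7 and U26 at week 26. QALYs are the area under straight lines joining the measured points.

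**Formulas.**
- Through week 7: (0.5 × 7 × U7 + 0.5 × (U7 + U26) × 19) / 52
- Two points only: (0.5 × 26 × U26) / 52 = 0.25 × U26

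**Results, with D the size of the gain.**

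| Time course | U7 | U26 | Through week 7 | Two points | Error of two points |
|---|---|---|---|---|---|
| Reached by week 7, maintained | D | D | (3.5 + 19)D/52 = 0.433D | 0.250D | 42% too low |
| Reached by week 7, halved by month 6 | D | D/2 | (3.5 + 14.25)D/52 = 0.341D | 0.125D | 63% too low |
| Reached by week 7, fully faded | D | 0 | (3.5 + 9.5)D/52 = 0.250D | 0 | all lost |
| Half reached by week 7, full at month 6 | D/2 | D | (1.75 + 14.25)D/52 = 0.308D | 0.250D | 19% too low |
| Linear growth to month 6 | 7D/26 | D | 0.250D | 0.250D | none |
| Nothing by week 7, full at month 6 | 0 | D | 9.5D/52 = 0.183D | 0.250D | 37% too high |

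In the maintained case, cost per QALY is inflated by 0.433/0.250, about 1.7-fold.

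**Scale.** The article gives no D. For illustrative values of 0.02, 0.05 and 0.10, the maintained case gives 0.0050 against 0.0087, 0.0125 against 0.0216, and 0.0250 against 0.0433 QALY. The shortfall is thus about 0.004 to 0.018 QALY.

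**A different convention.** Applying the month-6 difference to all 26 weeks gives 26/52 = 0.5 × U26. Against the path through week 7, that is 0.5D against 0.433D if maintained (about 16% too high), 0.25D against 0.341D if halved (about 27% too low), and still 0 against 0.250D if fully faded. The choice of convention can reverse the sign of the error, and two-point data cannot say which convention is right.

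**The case against.** A reader might infer that the plan will understate the QALY gain under its own hypothesis and so reach a wrong conclusion on cost-effectiveness. The documents do not support that, for four reasons.

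- The direction depends on a rule that the article does not state. Straight-line interpolation understates the maintained case, whereas carrying the month-6 value back overstates it.
- The hypothesised time course is for perceived stress. Nothing is said about when utility should change. EQ-5D has one anxiety/depression item among five, the others being mobility, self-care, common activities and pain/discomfort, so it need not follow the stress scale week by week.
- A late gain is plausible. The training has seven sessions with one or two log-ins a week recommended, so a once-weekly user finishes at about week 7, and an optional booster follows four weeks after completion. Two points would then overstate the gain. The fading cases, which give the largest losses, run against the expectation that the effect is maintained.
- With straight-line interpolation, the error in the maintained case works against the intervention. No cost or willingness-to-pay threshold is given, so a reversed conclusion is not shown.

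It can also be said that nothing here is contradictory. The cost questionnaire and the quality-of-life measures share one schedule, which looks deliberate, and the full set of questionnaires already takes about 30 minutes.

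All of this limits how strongly the point can be put, but it does not remove it. The 7-week dash is a stated feature of the schedule. A separate analysis plan can choose a formula but cannot recover a utility that was never collected. Bootstrapping resamples the same two time points, and the planned multi-way sensitivity analysis cannot supply the missing value.

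**Conclusion.** The point holds as a design weakness in the cost-utility analysis. The 6-month QALY difference rests on baseline and month 6 and may be misestimated by an amount that the trial's own data cannot reveal. Across the time courses examined under linear interpolation, the error runs from losing the whole gain to overstating it by about 37%. For the time course hypothesised for stress it is a 42% understatement. Of the patterns tabulated, only linear growth to month 6 leaves no error.

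These figures assume straight-line interpolation, balanced baselines and a particular path for utility, none of which the article fixes. The path through week 7 is itself only a three-point approximation. Because D is unknown, the proportions are the result and the absolute QALY values are illustrations.

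The primary outcome, the symptom outcomes and the sample size are untouched, as is any cost-effectiveness ratio that does not use QALYs. The change is still worth making, because cost-utility is a stated aim and the Discussion presents the economic evaluation as a strong advantage of the study.

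**What to change.** In Table 2, tick EQ-5D at T2 for both arms; adding SF-12 there is optional. In the Economic evaluation section, state that QALYs over the controlled 6 months are the area under the utility curve through T1, T2 and T3.

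The cost is five items and a visual analogue scale, plus twelve items if SF-12 is included, at an online assessment that both arms already complete: a minute or two of extra burden. No new contact is needed.

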### Statistical analyses

Analyses will be conducted and reported according to the Consolidated Standards of Reporting Trials (CONSORT) statement regarding eHealth [79,80].

#### Clinical analyses

Data will be analyzed on an intention-to-treat basis. Additionally, completers-only and per-protocol analyses will be carried out. Missing data will be dealt with following the recommendations of Little and Rubin [81] and Schafer [82]. We will use repeated measurements analysis of variance to examine differences in the primary and secondary outcome measures between the two groups, and we will compute standardized effect sizes (Cohen’s d). The number needed to treat (NNT) and the clinical significance in terms of a reliable change and recovery rates will be investigated using the method of Jacobson and Truax [83].

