### Inclusion and exclusion criteria

The target group will consist of stressed employees from the general working population aged 18 years or older. Inclusion criteria will include current employment and a distinct level of perceived stress as indicated by scores of 22 and above on the Perceived Stress Scale (PSS-10). This cut-off was chosen to select participants with a marked level of subjective stress as identified by one standard deviation (SD = 6.2) above the mean (PSS-10 = 15.3) in a large working population [42]. Applicants with an elevated risk of suicide (Beck Suicide Item > 1) and applicants that self-report having been diagnosed with psychosis or dissociative symptoms in the past will be excluded. For applicants that are at risk for suicide we follow a standardized procedure. These applicants will be advised to seek help via their general practitioner, the local psychiatric emergency room or an official emergency number, and the relevant information and telephone numbers will be provided by email.

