### Randomization

The randomization will be carried out by an independent researcher using a web-based randomization program (randomisation.eu) that will be set to allocate participants (N=264) into each group at a ratio of 1:1.

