### Sample size

We aim to include 264 participants to produce a statistically relevant effect size of d = .35, a power (1-β) of 80% and an alpha of .05 (two-tailed test) for intention-to-treat analysis using PASS 12. A comprehensive meta-analysis on traditional face-to-face interventions for work-related stress yielded an overall combined effect size of d=.34, whereby the results for web-based stress-management interventions are mixed, ranging from non-significant [17] to moderate effect sizes [16]. Therefore, we aim for an effect size of d=.35.

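### The repeated-measures ANOVA for perceived stress names no baseline covariate; adjusting the 7-week comparison for baseline PSS would be more precise at no cost

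*Protocol article*

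**What the plan says.** The Clinical analyses section of the protocol article fixes the method: "We will use repeated measurements analysis of variance to examine differences in the primary and secondary outcome measures between the two groups". It names no covariate, does not list the levels of the time factor, and does not say which term carries the primary claim.

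The hypothesis, under Aims of the study and hypotheses, is that the intervention group "will show a greater reduction in the primary outcome perceived stress from pre-test to post-test compared to a waitlist control group", with the effect then maintained over six months.

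Other text that bears on the point:

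- Sample size: "We aim to include 264 participants to produce a statistically relevant effect size of d = .35", with "a power (1-β) of 80% and an alpha of .05 (two-tailed test) for intention-to-treat analysis using PASS 12".
- Inclusion and exclusion criteria: entry needs "scores of 22 and above on the Perceived Stress Scale (PSS-10"), a cut-off set one standard deviation above a working-population mean.
- Table 2: PSS is measured in both groups at screening (T0), baseline (T1), 7 weeks (T2) and 6 months (T3).
- Clinical analyses, on incomplete data: "Missing data will be dealt with following the recommendations of Little and Rubin [81] and Schafer [82"]. The main analysis is intention-to-treat, and the completers-only analysis is additional.

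**The concern.** A repeated-measures ANOVA with baseline among its time levels treats the pre-randomisation score as an outcome. With two levels (T1, T2) the group-by-time test is the t-test on change from baseline. That test subtracts the whole baseline score, whereas regression on baseline subtracts only the part that predicts the outcome. In a randomised trial both are unbiased for the treatment effect, but the regression has the smaller variance.

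With three levels (T1, T2, T3) the group-by-time test has 2 degrees of freedom. It can then be significant because of a difference that appears only at six months, which is not the pre-to-post claim.

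What is at stake is precision and a clear link between test and hypothesis. Validity is not in question. The baseline score is collected anyway, so the precision is free.

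**Working it through.** **Inputs from the article:** N = 264, 1:1 (132 per arm), d = .35, two-sided alpha .05, 80% power. **Assumed:** d is in units of the 7-week SD, there are no losses, and r is taken over a range because the article gives none.

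**1. The stated sample size.** Normal approximation: n per arm = 2(1.960 + 0.842)²/0.35² = 128.1, so 129, total 258. The exact t-test needs 130 per arm, total 260. At 132 per arm the exact power is 80.9%. The figure of 264 therefore fits a plain two-group comparison with no baseline term and no allowance for dropout.

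**2. Change score against ANCOVA, equal variances.** In units of the 7-week variance, the change score has variance 2(1 − r) and ANCOVA has 1 − r². Their ratio is 2/(1 + r), above 1 for every r below 1. Power is noncentral t with effect .35/√variance; N is by the normal approximation.

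| r | Power, change score | Power, ANCOVA | Variance ratio | N for 80%, change score | N for 80%, ANCOVA |
|---|---|---|---|---|---|
| .3 | 66.8% | 84.4% | 1.54 | 360 | 234 |
| .4 | 73.4% | 87.1% | 1.43 | 308 | 216 |
| .5 | 80.9% | 90.5% | 1.33 | 258 | 194 |
| .6 | 88.6% | 94.3% | 1.25 | 206 | 166 |
| .7 | 95.5% | 97.8% | 1.18 | 154 | 132 |

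**3. Allowing for selection on PSS.** Selection lowers r, but it also lowers the baseline variance, which helps the change score. I truncated a normal T0 score at +1 SD, which leaves 0.199 of its variance (k = 1 − 0.199 = 0.801). Let a, b and c be the T0–T1, T1–T2 and T0–T2 correlations before selection. After selection, var(T1) = 1 − k·a², var(T2) = 1 − k·c² and cov(T1,T2) = b − k·a·c. All correlations are assumed: a from .7 to .9, b from .5 to .7, c either a·b or .9·b. Here d is in units of the T2 SD after selection.

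- Example, a = .9, b = .5, c = .45: var(T1) = 0.351, var(T2) = 0.838, cov = 0.176, r = .32. Change variance = 0.351 + 0.838 − 2(0.176) = 0.838 after rounding, equal to var(T2), so power is 80.9%. ANCOVA gives 84.9%.
- Weakest case for the change score, a = .7, b = .5, c = .45: var(T1) = 0.608, var(T2) = 0.838, cov = 0.248. Change variance is 0.950 and power 75.8%. ANCOVA residual variance is 0.838 − 0.248²/0.608 = 0.737 and power 85.6%.
- Over all 18 settings, change-score power runs from about 76% to 92% and is below 80% in two. ANCOVA runs from about 85% to 95%. The gap is about 2 to 10 points.

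**4. If three levels were tested jointly.** Under compound symmetry the F test has 2 and 524 df, with noncentrality 66·Σ(e − ē)²/(1 − r), where e is the group difference at each time.

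- Full effect at T2 and T3: 69.7%, 84.3% and 97.4% at r = .3, .5 and .7.
- Effect halved by T3: 56.4%, 72.0% and 91.7%.
- Effect only at T3, none at T2, r = .4: Σ(e − ē)² = 0.0817, noncentrality 66 × 0.0817/0.6 = 8.98, so the test is significant 76.7% of the time although the pre-to-post effect is zero.

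**The case against.** The strongest reply is that nothing here is an error. Randomisation makes the change-score estimate unbiased, the sample size reproduces, and a two-level group-by-time test is exactly the pre-to-post hypothesis. All of that stands, and it limits the point to an improvement in efficiency. Three stronger readings are tempting and should not be drawn.

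- **That the plan needs complete cases, or conflicts with intention-to-treat.** Classical repeated-measures ANOVA needs a full set of scores per person, so a reader might infer this. The same section, however, plans missing-data handling and makes completers-only an additional analysis. The ANOVA can be run on completed data, and the exact procedure may be left to the full plan.
- **That the primary test is an omnibus interaction.** The article names neither the time levels nor the tested term, so this holds only if T1, T2 and T3 are tested together. Such a test is not always weaker either: with a sustained effect and r = .5 it has 84.3% power against 80.9% for the two-level test.
- **That the trial misses its 80%.** The equal-variance figures at low r suggest this. They leave out the smaller baseline variance that the entry cut-off produces. With it included, change-score power lies on both sides of 80%, mostly above.

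**Conclusion.** The point holds as an optional improvement. The article fixes a method without baseline adjustment; on the usual reading it is valid and unbiased but less precise than adjusting for baseline PSS at any r below 1. The gain at N = 264 and d = .35 is about 18, 10 and 2 power points at r = .3, .5 and .7 with equal variances, and about 2 to 10 points when selection at PSS-10 of 22 or more is modelled. No shortfall from the stated 80% is demonstrated.

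These sizes rest on assumed correlations, normality, no losses, d in units of the 7-week SD, and truncation at +1 SD of the screening distribution. If applicants are already more stressed than the reference working population, the truncation is milder and the result moves toward the equal-variance table. The direction of the gain depends on none of this. The mismatch with the pre-to-post hypothesis is conditional on a joint three-level test.

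**What to change.** - Make the primary estimate the between-group difference in 7-week PSS adjusted for T1 PSS, with a 95% CI. Obtain it from an ANCOVA, or from a baseline-adjusted or constrained-baseline mixed model over T2 and T3.
- Keep all randomised participants through the missing-data handling already planned. This matters because a model with only T2 and T3 as outcomes would otherwise drop anyone with no post-baseline score.
- Treat the adjusted six-month contrast from the same approach as the test of maintenance.
- Use the same approach for secondary outcomes measured at T1, T2 and T3.
- Keep the repeated-measures ANOVA as a sensitivity analysis, stating its time levels and the term tested.

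The cost is a change of wording in the analysis section. It needs no new data, visits or participants.
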